### Randomization

The randomization list was generated by using the website Randomization.com . The permuted block method of randomization for a block size of three was used. According to this list patients were allocated to each of the three groups in the trial: intravenous antibiotics, oral antibiotics and placebo.

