### Sample size

The frequency rate of meningitis among our traumatic pneumocephalus patients was 21.5% (*p*1). What we expect to be an intended (or at least acceptable) effect of the prophylactic antibiotics is 5 %(*p*2) frequency of meningitis in the patients with antibiotics. To detect this difference with a sensitivity of 80% and an error probability of 5%, at least 62 patients per randomization group will be required using the following formula:

*n *= 7.84 * [*p*1(1 - *p*1) + *p*2 (1 - *p*2)]/[*p*_1 _- *p*_2_]^2^

Considering only comparing the placebo group with each one of the antibiotics group, our sample size should be at least 186 cases. To account for the possibility of loss to follow-up, our estimated sample size is 200 cases.

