### Blinding

Since providing both the antibiotics and placebo in identical containers for participating centers is not practically possible for us, this study is not double-blinded.

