### Study design

The patients should be observed in the hospital, until occurrence of meningitis or at least 7 days after trauma. In the case of concomitant Cerebrospinal Fluid (CSF) leakage and need for close observation in the hospital, they will be hospitalized until recovery from leakage. After discharge the patients will be followed up until one month after trauma.

The following data is registered: age, sex, time interval between trauma and admission, time interval between admission and antibiotic therapy, the cause of trauma, GCS upon admission, intracranial air volume (at the time of admission and three days later), intracranial air location, presence of CSF rhinorrhea, CSF otorrhea, presence and location of the radiological signs of skull base fractures, presence and volume of the intracranial hemorrhage(at the time of admission and three days later), presence of meningitis, CSF findings, treatment and complications in the case of meningitis and one month follow-up note.

Intracranial air and hemorrhage volume are calculated in the CT scan using the formula *ABC*/2, where *A *is the greatest mass diameter by CT, *B *is the diameter 90° to *A*, and *C *is the approximate number of CT slices with mass multiplied by the slice thickness. In the case of air in the subarachnoid space, this formula is not easily applicable and an approximate volume is calculated and determined whether the volume is less than 10 cc or not [7].

The patients are divided into three groups; with intravenous antibiotics (IV), oral antibiotics (O) and placebo (P), according to the randomization list. In IV group, Ceftriaxone 2 grams BID plus oral placebo and in O group, Azithromycin 500 mg in the first day followed by 250 mg daily plus intravenous placebo for the rest will be continued for 7 days. Antibiotics should be started in less than 24 hours after trauma. Since antibiotics may mask the clinical presentation of the meningitis, these patients (IV and O) will remain hospitalized two more days for close clinical observation. In the case of meningitis, appropriate antibiotics are continued until patients' recovery. Corticosteroids should not be prescribed for the patients for any reason.

The physicians caring for the patients are not blinded to the regimen that is used.

Intracranial hemorrhages included subarachnoid hemorrhage, epidural and subdural hematoma and cerebral contusion or hematoma.

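### A fixed block of three for three arms, with treating physicians unblinded, lets up to one third of allocations be deduced before enrolment

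*Protocol article*

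**What the plan says.** The Randomization section names one block size: "The permuted block method of randomization for a block size of three was used". According to the list, "patients were allocated to each of the three groups in the trial: intravenous antibiotics, oral antibiotics and placebo". A block of three for three arms means one patient per arm in every block. The same section gives the source of the list: "The randomization list was generated by using the website Randomization.com".

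The Blinding section says that "this study is not double-blinded", because supplying drug and placebo "in identical containers for participating centers is not practically possible for us". The Study design section adds: "The physicians caring for the patients are not blinded to the regimen that is used". That section also describes an oral placebo in the intravenous arm and an intravenous placebo in the oral arm, but by its own statement these do not hide the arm from the treating physicians. The Discussion concedes the lack of double-blinding as a possible shortcoming and does not connect it with the block size.

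**The concern.** Three is the smallest possible block for three equal arms, so among permuted-block schemes it is the most predictable. Hiding the list does not cure this. The next arm is not read from the list but deduced from treatments already given in the open, and the block size is published.

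Prediction matters here because prognosis can be seen at entry. The Background names CSF rhinorrhea and intracranial hemorrhage as primary risk factors for meningitis, and intradural air and air volume above 10 cc as secondary ones. The exclusion criteria require a judgement on whether injuries are life-threatening, so a patient can be declined without breaking a written rule. If high-risk patients are withheld when placebo is foreseen, the placebo arm becomes healthier than the antibiotic arms and a real benefit is diluted. Selection on the other arms could push the result the other way.

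**Working it through.** **Inputs.** Block size 3, three arms (Randomization). Planned total: "our estimated sample size is 200 cases" (Sample size). Planned meningitis rates 21.5% without and 5% with antibiotics (Sample size).

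**The plan's own figure.** The article gives no figure for predictability; its only related figure is the sample size, used here for scale. Its formula gives 7.84 × [0.215 × 0.785 + 0.05 × 0.95] / 0.165² = 7.84 × 0.216275 / 0.027225 = 62.3. This agrees with the stated 62 per group (3 × 62 = 186, raised to 200). The point below concerns bias and leaves this calculation untouched.

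**Predictability as written.** For an observer who knows the block size and sees all earlier allocations on the list:

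- First place in a block: three arms possible, best guess right with probability 1/3.
- Second place: one arm ruled out, probability 1/2.
- Third place: two arms ruled out, probability 1.

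Share known with certainty = 1/3. Among 200 patients there are 66 complete blocks, hence 66 such allocations. Placebo comes last in one third of blocks on average: 66 / 3 = 22. Expected correct guesses = (1/3 + 1/2 + 1) / 3 = 61.1%, against 33.3% with no information.

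**If centres share one list.** The Blinding section implies more than one centre. As an assumption, let equal centres enrol independently from one list. The centre enrolling the third patient of a block also enrolled both earlier ones with probability (1/2)² = 1/4 for two centres and (1/3)² = 1/9 for three. Certain allocations are then at most:

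- two centres: 1/3 × 1/4 = 1/12, about 17 of 200;
- three centres: 1/3 × 1/9 = 1/27, about 7 of 200.

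Even these need the centre to know where each block begins. With a separate list per centre, or a single centre, the full one third applies.

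**Scale against the outcome.** With about 66 per arm, the planned rates imply 0.215 × 66 = 14 meningitis cases on placebo and 0.05 × 66 = 3 on each antibiotic. Each expected placebo case withheld, and replaced by a patient who stays free of meningitis, lowers the placebo rate by 1/66 = 1.5 percentage points. The planned difference is 16.5 points.

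**Alternatives.** For a fixed block with k patients per arm, the expected number of certain allocations per block is the sum over j = 1 to k of 3 × C(k, j) / C(3k, j). For k = 2 this is 1 + 0.2 = 1.2, and 1.2 / 6 = 20.0%. For k = 3 it is 1 + 0.25 + 0.036 = 1.286, and 1.286 / 9 = 14.3%. The fixed-block guess rates come from complete enumeration. The mixed scheme was simulated (400 lists of 198) with an observer who sees every earlier allocation and knows the set of sizes but not the size of each block.

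| Scheme | Certain in advance | Guessed correctly |
|---|---|---|
| Fixed 3 (as written) | 33.3% | 61.1% |
| Fixed 6 | 20.0% | 56.1% |
| Fixed 9 | 14.3% | 53.2% |
| Random mix of 6 and 9 | about 5% | about 54% |
| Simple randomization | 0% | 33.3% |

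**The case against.** The strongest reply is that predictability does harm only if the person who enrols sees the sequence, and the article does not establish that. It says that physicians caring for patients are unblinded, not that they recruit. With several centres on one list, most of the 66 certain allocations disappear. This stands, and it makes one third a ceiling. It does not remove the concern, because nothing in the text rules out a single list seen by recruiters, or one list per centre.

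A reader might infer that every third allocation is in fact known, or that patients were in fact selected by arm. The documents support neither: the first depends on the list structure, and no selection is shown.

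A reader might also infer that the analysis could do nothing about such selection. That goes too far. Study design records rhinorrhea and the admission volumes of air and hemorrhage, and Statistical analysis plans logistic regression adjusted for other risk factors. Selection on those recorded factors can be partly adjusted for. Selection on unrecorded judgement cannot, and the unadjusted chi-square test corrects for nothing.

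Two further points narrow the mechanism. Deferring a patient is hard, because antibiotics must start within 24 hours of trauma; declining one remains possible. And withholding patients because placebo is foreseen with certainty concerns about 22 allocations, not 66.

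Finally, who holds the list and how assignments are released are details that an article may leave to the full protocol. Their absence is no part of this point.

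**Conclusion.** The point holds as a weakness in a stated design rule. With blocks of three for three arms and unblinded treating physicians, up to 33% of allocations (about 66 of 200, about 22 of them placebo) can be deduced, and up to 61% guessed correctly. These figures assume that a recruiter knows the block size and sees consecutive allocations on one list. Under the shared-list assumption above, certain allocations fall to at most about 17 of 200 with two centres and about 7 with three.

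So the opportunity for selection is established; its actual extent is not, and neither is any resulting bias. Because the size depends on facts about centres and recruiters that the article does not give, while the remedy is cheap, this is something that should be fixed rather than a defect that by itself invalidates the trial.

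**What to change.** Generate the list with block sizes varying at random between 6 and 9, and do not disclose the sizes to recruiters. The article reports list generation in the past tense, so a list already exists. If recruitment has begun, replace only the unused part and record this as a protocol change; patients already allocated keep their assignments.

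The effect is large for certain allocations (33% to about 5%, roughly 66 to 10 of 200) and modest for guessing (61% to about 54%). The guessing figure is for an observer who knows that sizes 6 and 9 are in use.

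The cost is small: a new list, a documented change if the trial is under way, and a possible final imbalance. A list cut off inside a block of 9 can leave two arms at most 3 patients apart, against 1 with blocks of three.

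Separate lists per centre should not be adopted as a remedy for predictability. Compared with one shared list, they let each centre see its whole sequence. If per-centre lists are wanted for balance, the varying block sizes matter more.

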### Blinding

Since providing both the antibiotics and placebo in identical containers for participating centers is not practically possible for us, this study is not double-blinded.

### Study design

The patients should be observed in the hospital, until occurrence of meningitis or at least 7 days after trauma. In the case of concomitant Cerebrospinal Fluid (CSF) leakage and need for close observation in the hospital, they will be hospitalized until recovery from leakage. After discharge the patients will be followed up until one month after trauma.

The following data is registered: age, sex, time interval between trauma and admission, time interval between admission and antibiotic therapy, the cause of trauma, GCS upon admission, intracranial air volume (at the time of admission and three days later), intracranial air location, presence of CSF rhinorrhea, CSF otorrhea, presence and location of the radiological signs of skull base fractures, presence and volume of the intracranial hemorrhage(at the time of admission and three days later), presence of meningitis, CSF findings, treatment and complications in the case of meningitis and one month follow-up note.

Intracranial air and hemorrhage volume are calculated in the CT scan using the formula *ABC*/2, where *A *is the greatest mass diameter by CT, *B *is the diameter 90° to *A*, and *C *is the approximate number of CT slices with mass multiplied by the slice thickness. In the case of air in the subarachnoid space, this formula is not easily applicable and an approximate volume is calculated and determined whether the volume is less than 10 cc or not [7].

The patients are divided into three groups; with intravenous antibiotics (IV), oral antibiotics (O) and placebo (P), according to the randomization list. In IV group, Ceftriaxone 2 grams BID plus oral placebo and in O group, Azithromycin 500 mg in the first day followed by 250 mg daily plus intravenous placebo for the rest will be continued for 7 days. Antibiotics should be started in less than 24 hours after trauma. Since antibiotics may mask the clinical presentation of the meningitis, these patients (IV and O) will remain hospitalized two more days for close clinical observation. In the case of meningitis, appropriate antibiotics are continued until patients' recovery. Corticosteroids should not be prescribed for the patients for any reason.

The physicians caring for the patients are not blinded to the regimen that is used.

Intracranial hemorrhages included subarachnoid hemorrhage, epidural and subdural hematoma and cerebral contusion or hematoma.

The diagnosis of bacterial meningitis is based upon CSF findings (increase in leukocyte count, decrease in CSF glucose [<60% of the level simultaneously measured in blood] increase in the CSF protein > 45 mg/dL and positive CSF smear or culture) in patients with compatible clinical findings (fever, headache, nausea and vomiting, change in the level of consciousness and/or meningismus not explainable with other causes). Probable meningitis is defined when positive CSF smear or culture is not available. In rare cases with relative contraindications for lumbar puncture (accompanying intracranial hemorrhage and clinically suspected raised intracranial pressure), the possible diagnosis of meningitis is based upon clinical findings and ruling out other causes.

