### Selection of drugs

In posttraumatic meningitis after traumatic pneumocephalus, the microorganisms enter the CSF from the outside mainly air sinuses. This is the reason why pneumococci are the major causative microorganisms. In order to prevent posttraumatic meningitis in pneumocephalus patients, we should either clear the air sinuses from the potential microorganisms or make the CSF defense strong enough to control those pathogenic microorganisms that have passed the blood brain barrier. This simple strategy has not worked favorably so far. There might be various reasons. We thought that the dosage of the antibiotics might have been less than enough due to lack of inflammation of the blood brain barrier. So based on the most common microorganisms in microbiological studies of the posttraumatic meningitis it has been decided to administer antibiotics with full antimeningitic dosage (2 grams Ceftriaxone twice a day) prophylactically.

Another reason for inability of the previous studies to demonstrate the efficacy of prophylactic antibiotics might have been lack of enough coverage of the normal flora of the air sinuses. These sinuses should be considered the potential source of the secondary infection in majority of cases. In order to cover these, we selected Azithromycin as an oral regimen. Penetration of drugs into the cerebrospinal fluid, minimal gastrointestinal side effects, patient tolerance and cost-effectiveness of medications were other important factors in selection of drugs.

In our previous studies meningitis happened almost always in the first week post trauma, so both regimens are continued for 7 days.

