### Outcome measures

#### Primary outcome measure

The frequency of bacterial meningitis in IV, O and P groups

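### The primary outcome, read literally, counts only smear- or culture-positive meningitis, which may be harder to confirm on study antibiotics and so could favour those arms

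*Protocol article*

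**What the plan says.** The Primary outcome measure section names one endpoint: "The frequency of bacterial meningitis in IV, O and P groups". It does not mention levels of diagnostic certainty.

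The diagnostic paragraph that closes the Study design section sets out three levels:

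- **Bacterial meningitis:** compatible clinical findings, raised CSF leukocytes, low CSF glucose, "increase in the CSF protein > 45 mg/dL and positive CSF smear or culture".
- **Probable:** "Probable meningitis is defined when positive CSF smear or culture is not available".
- **Possible:** in rare cases with a relative contraindication to lumbar puncture, "the possible diagnosis of meningitis is based upon clinical findings and ruling out other causes".

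No section says which of these levels enter the primary outcome.

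Three other statements bear on the point. The Selection of drugs section explains the decision to "administer antibiotics with full antimeningitic dosage" in the intravenous arm, and gives the early timing of meningitis in the group's previous studies (almost always the first week) as the reason for continuing both regimens for 7 days. The Study design section concedes that "antibiotics may mask the clinical presentation of the meningitis". It also says that the treating physicians know the regimen.

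**The concern.** The endpoint and the strictest diagnostic level share a name, and that level needs microbiological confirmation. A patient with the full clinical and CSF picture but no positive smear or culture is called probable and, on a literal reading, drops out of the numerator.

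Whether a case is confirmed may depend on the arm. In the antibiotic arms, most diagnostic lumbar punctures would be taken while the patient is on an active drug. In the placebo arm they would not. If that lowers the smear or culture yield, the same disease is counted more often on placebo than on antibiotic. The trial could then report prevention where there was only loss of confirmation, and it could do so on its only primary outcome.

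**Working it through.** **Inputs from the protocol article.** Meningitis rate p1 = 21.5%, target rate p2 = 5%, 80% power, 5% error, 62 per group, 186 in total, raised to 200 (Sample size); chi-square test for categorical variables (Statistical analysis).

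**The plan's own figure.** n = 7.84 × [0.215 × 0.785 + 0.05 × 0.95] / (0.215 − 0.05)² = 7.84 × 0.216275 / 0.027225 = 62.28. This agrees with the stated 62, and 3 × 62 = 186. With 200 patients in three arms, 200 / 3 = 66.7, so 66 per arm is used below.

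**Assumptions not in the documents.**

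- No true effect: 21.5% true meningitis on placebo and on antibiotic.
- The 21.5% is treated as all true cases. The protocol does not say which diagnostic levels it includes.
- The yield, meaning the share of true cases with a positive smear or culture, is 80% on placebo and varies on antibiotic.
- Only confirmed cases count.

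**Formulas.** Observed rate = true rate × yield. With no true effect, the apparent risk ratio is the yield on antibiotic divided by the yield on placebo. The chance of a false significant benefit comes from exact enumeration of two binomial counts, using the uncorrected chi-square test at two-sided 5% and counting only results in favour of the antibiotic.

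The observed placebo rate is 0.215 × 0.80 = 17.2%.

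| Yield on antibiotic | Observed rate on antibiotic | Apparent risk ratio | Chance of false benefit |
|---|---|---|---|
| 80% (equal) | 17.2% | 1.00 | 2.4% |
| 75% | 16.1% | 0.94 | 3.5% |
| 70% | 15.1% | 0.88 | 5.0% |
| 60% | 12.9% | 0.75 | 9.8% |
| 40% | 8.6% | 0.50 | 30.9% |

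**Sensitivity to the assumptions.** With 62 per arm and a placebo yield of 90%, antibiotic yields of 80%, 70%, 50% and 30% give chances of 4.7%, 8.7%, 25.8% and 58.4%. The direction is the same and the size depends almost wholly on the assumed gap.

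**If probable cases also count.** A missing positive smear or culture no longer moves a case out of the outcome. With 21.5% observed in both arms, the chance of a false benefit is again about 2.4% (62 per arm).

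**The case against.** The strongest reply is that the bias is conditional. No section excludes probable cases. The sentence that creates the probable level shows that culture-negative cases were foreseen, and the Sample size section and the list of registered data speak simply of meningitis. If all levels count, this mechanism largely disappears. That stands, and it rules out the stronger conclusion a reader might draw, that the primary outcome is certainly biased. It does not remove the point: the defined term matches the endpoint's name and points towards confirmed cases only. Because the article sets out the case definition in detail, the problem lies in what that definition does and is not merely a detail left to a longer document.

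A reader might also infer that the protocol admits the drugs suppress smear or culture. It does not. It concedes only possible masking of the clinical presentation, which is a different mechanism. Lower yield on treatment is plausible, but its size is undocumented. A small gap does little harm: 80% against 75% raises the chance of a false benefit only from 2.4% to 3.5%. Nor do the documents support any particular difference in yield between ceftriaxone and azithromycin.

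The net direction of all ascertainment effects is also unsettled. After the masking remark the plan adds that "these patients (IV and O) will remain hospitalized two more days for close clinical observation", which could raise detection in those arms. That is a separate difference in ascertainment. It cannot be relied on to offset lost confirmation, and longer observation does not make a negative culture positive.

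Finally, requiring confirmation has a real rationale when physicians are unblinded, because clinical findings must be judged not to have another explanation. This stands as a cost of the remedy.

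**Conclusion.** The point holds in conditional form. Read literally, the plan limits its primary outcome to smear- or culture-positive meningitis and never says that probable cases count. If only confirmed cases are counted, and if yield is lower on study antibiotics, the comparison with placebo leans towards the antibiotics even with no true effect.

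Under the stated assumptions (21.5% true meningitis in both arms, 66 per arm, 80% yield on placebo, 75% down to 40% on antibiotic), the chance of a false significant benefit is about 3.5% to 31%, against 2.4% with equal yields. The yields are illustrative. The documents support the mechanism and its direction for this one source of bias. They do not support a specific size.

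**What to change.** State in the Primary outcome measure section that the outcome is definite plus probable meningitis: compatible clinical findings together with the CSF leukocyte, glucose and protein criteria already given, applied identically in all three arms whatever the smear or culture result.

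Prespecify two sensitivity analyses: confirmed cases only, and definite plus probable plus possible cases.

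The change is one of wording. CSF findings are already registered, so no new data are needed. The price is lower diagnostic specificity, and the loss may not be equal across arms because more weight falls on the clinical judgement of unblinded physicians. The confirmed-only analysis shows how far the result depends on this. Having someone unaware of allocation classify the cases would strengthen the definition. The change does not deal with clinical masking, since compatible clinical findings are still required.
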